### Patient inclusion criteria

1) Males and females ≥ 45 years of age and

2) Smoker or ex-smoker (with at least ten PY) and

3) Obstruction in spirometry FEV_1_/FVC < 0.7

### Patient exclusion criteria

1. No obstruction in spirometry (FEV1/FVC ≥ 0.7) or

2. Patients with history of asthma or hay fever or

3. Other concomitant pulmonary disease or

4. Patients with malignancies of any other system and/or other severe disease with an estimated life expectancy of less than six months or

5. Insufficient German language skills or

6. Patients who contact the practice for emergencies only or as a substitute practice

The flow chart of GP and patient recruitment of the study is shown in Figure 2.

**Figure 2 F2:**
[figure not shown]
Study flow chart.

### Clinical interventions/guideline adherence

With the ‘QualiCCare’ intervention, we reach out to implement the recommended key clinical processes in primary care for patients with diagnosed COPD namely: smoking cessation counseling, yearly influence vaccination, counseling to increase motivation for physical activity and pulmonary rehabilitation, self-management education with a written action plan to do the right thing at the right time in case of an exacerbation; appropriate pharmacologic treatment for stable and exacerbated COPD, and proactive, collaborative COPD care.

### Implementation program

#### Instruction of the GPs and practice assistants in the intervention group

Physicians randomized into the intervention group get a ‘QualiCCare’ training workshop designed to educate professionals on the guidelines, but also and particularly, governing professional behavior by feedback, reminders and pathways that help to change their attitudes and care behavior [23-25]. Based on behavioral and learning theory [26], ‘QualiCCare’ intervention not only tries to increase knowledge but also internal motivation and decision- making by stimuli and resources and by written instruments that guide evidence-based decision support.

The education sessions will actively involve GPs and practice assistants with tasks and responsibilities and also, by demonstrating them (by interactive teaching, case vignettes and role plays), ways on how evidence-based tasks could be incorporated into their daily work.

Three instruments (A-C) have been developed based on a review of international and national guidelines and in collaboration with the Swiss Respiratory Society, Swiss Societies of Internal and General Medicine and College of Primary Care Medicine, with a specific focus on primary care circumstances and needs. These instruments will be introduced to the intervention group as working tools for daily practice to support decision-making and adherence with recommended COPD care.

A. The Swiss COPD quintessence for primary care is a clinical guideline for GPs which is consistent with international guidelines for COPD [27] and the newly published Swiss COPD guideline [6], but more comprehensive and summarizing the key elements of COPD management for Swiss primary care [28].

B. The COPD pocket guide contains evidence-based information, assessment tools (MRC, CAT, STS), opinion sheets (early diagnosis, smoking cessation advice), treatment algorithm and decision aids for the key COPD elements: Confirm diagnosis, Optimize symptoms, Prevent deterioration, and Develop network and self-management support. The pocket guide also contains addresses and links to useful information as well as for specialist support, pulmonary rehabilitation and community resources offering, for example, smoking cessation and patient education.

C. The Primary care COPD Care bundle is something new for the primary care setting. So far, experience for COPD only exists for discharge care bundles for COPD patients hospitalized with acute exacerbations. The implementation of a discharge care bundle improved adherence with optimum health care practice [22]. Our primary care COPD care bundle comprises a short list of evidence-based practice items to be implemented into primary care for patients with COPD. It can function as a reminder and as a checklist of all necessary activities that can be ticked as performance control. It is expected to function as a stimulus for increased guideline adherence and internal motivation for behavior change.

Bundle items selected for primary care are:

1. Identify COPD in a smoker or ex-smoker (with at least ten PY) with symptoms (cough, sputum or dyspnea).

2. If the patient is still a smoker, offer smoking cessation assistance.

3. Motivate for physical activity and consider/refer for pulmonary rehabilitation.

4. Motivate for influenza vaccination.

5. Offer appropriate pharmacologic treatment for stable and exacerbated COPD.

6. Demonstrate and check correct use of inhalers.

7. Give written information about COPD including Lunge Zürich self-management booklet and an action plan.

8. Offer proactive follow-up and integrated services (for example follow-up, feedback and scheduling and ‘navigation’ functions by the trained practice assistant, arranging appointments, and connecting patients to internal and external providers and resources).

A specialized and experienced team of a pneumologist and a respiratory physiotherapist and master trainer will hold the ‘QualiCCare’ training workshop (half a day session). The three dimensions knowledge, skills and behavior in COPD management are addressed with consideration of the COPD care bundle items.

A ‘QualiCCare’ refresher course will be held six months after the first training workshop.

### Outcomes

#### Primary outcome

Difference in ‘quality of care process’ (total increase in performed measures/fulfilled indicators) after one year between COPD patients in the intervention and control group as reported by the patient (described below).

#### Secondary outcomes

a. Percentage of COPD patients with FEV1 < 60% and/or ≥ two exacerbations who received

• advice to participate in pulmonary rehabilitation

• referral to pulmonary rehabilitation

• a written action plan for exacerbation management

• proactive follow up and integrated services (arrangement for follow up and referrals)

b. Quality of life (CAT)

c. Aggregate measure for ‘quality of care process’ reported by the GPs

Details on the purpose defined, aggregate outcome measure (primary outcome and secondary outcome b):

Every process indicator will get a rating of 1, when performed (or done) and 0 when not performed. The range of the primary outcome will be from 0 to a maximum of 9, the range of the secondary outcome - applicable only for a subgroup of patients - will be 0 to a maximum of 13:

Indicators for the primary outcome:

1. Smoking cessation advice

2. Smoking cessation intervention

3. Influenza vaccination

4. Assessment of physical activity

5. Advice for physical activity

6. Assessment of exacerbation frequency

7. Appropriate pharmacological treatment: (no inhaled corticosteroids in patients with FEV1 > 50% and < two exacerbations/year)

8. Instruction in correct inhalation technique

9. Information and patient education: additional indicators for the secondary outcome: COPD patients with FEV1 < 50% or ≥ two exacerbations

10. A written action plan for exacerbation management

11. Advice to participate in pulmonary rehabilitation

12. Referral to pulmonary rehabilitation

13. Proactive follow-up and integrated services

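### Indicator 7 is defined only for patients outside the subgroup that gets the 13-item score; judged at one time point it is a constant there, and the stated 0–13 range is not attainable

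*Protocol article*

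**What the plan says.** All the relevant wording stands in the Protocol article, Outcomes, under Secondary outcomes.

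- Scoring rule: "Every process indicator will get a rating of 1, when performed (or done) and 0 when not performed". It has no third category.
- Primary score, indicators 1 to 9: "The range of the primary outcome will be from 0 to a maximum of 9".
- Indicator 7: "Appropriate pharmacological treatment: (no inhaled corticosteroids in patients with FEV1 > 50% and < two exacerbations/year".
- Indicators 10 to 13 are introduced as "additional indicators for the secondary outcome: COPD patients with FEV1 < 50% or ≥ two exacerbations".
- Resulting score: "the range of the secondary outcome - applicable only for a subgroup of patients - will be 0 to a maximum of 13".
- Secondary outcome a reports the same four added indicators as percentages, but its population is "Percentage of COPD patients with FEV1 < 60% and/or ≥ two exacerbations who received" and its cut-off is therefore 60%.

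The entry criterion is "Obstruction in spirometry FEV_1_/FVC < 0.7", with no limit on FEV1 itself, so patients on both sides of either cut-off are enrolled. The Data analysis section adds that each indicator may also be analysed on its own as a yes/no outcome by logistic regression.

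**The concern.** The condition inside indicator 7 and the condition for entering the 13-item score look like opposites. If they are, indicator 7 has no stated criterion for anyone who receives that score. Its value then depends on a coding convention and not on the patient's treatment.

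Three things are at stake. The article prints a range that the score cannot have. The subgroup score appears to cover pharmacotherapy, a named target of the programme, while carrying no information on it. And because the scoring rule is universal and binary, patients to whom indicator 7 does not apply would enter its separate analysis, and the primary score, with a 0 or a 1 that means nothing.

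**Working it through.** **1. The printed figure.** Nine primary indicators plus four added ones: 9 + 4 = 13. The 13 is reproduced as a count of listed items. The question is whether 0 to 13 is attainable.

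**2. The two groups.** Let F be FEV1 in percent and E the number of exacerbations, both judged at one time point.

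- Indicator 7 applies to A = {F > 50 and E < 2}.
- The 13-item score applies to S = {F < 50 or E ≥ 2}.
- The complement of S is {F ≥ 50 and E < 2}, which contains A. So A and S have no patient in common.
- Only F exactly 50 with E < 2 belongs to neither.

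Enumeration confirms this. A grid of F from 10 to 120 in steps of 0.5 and E from 0 to 6 has 221 × 7 = 1547 cells. S holds 80 × 7 + 141 × 5 = 1265, A holds 140 × 2 = 280, two cells are in neither (1265 + 280 + 2 = 1547), and the overlap is 0. The cells test the logic; they are not patient frequencies.

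**3. Attainable ranges in S.** Take the other indicators as free to be 0 or 1: twelve in the subgroup score, eight in the primary score.

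| Coding of indicator 7 | Subgroup score | Primary score, same patients |
|---|---|---|
| 0 or not applicable | 0–12 | 0–8 |
| Credited as 1 | 1–13 | 1–9 |
| Stated range | 0–13 | 0–9 |

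Neither coding gives the stated range for these patients.

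**4. The other cut-off.** With 60% in place of 50%, joined by 'or', the score's group has 100 × 7 + 121 × 5 = 1305 cells. The overlap with A is 19 × 2 = 38 cells: F above 50 and below 60, with 0 or 1 exacerbation. With 60% joined by 'and', the overlap is again 0.

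**5. Effect on the arm comparisons.**

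- *Subgroup score.* If indicator 7 equals a constant c for everyone, the arm difference is (m1 + c) − (m0 + c) = m1 − m0. There is no bias.
- *Indicator 7 alone.* Let q be the share of patients to whom it does not apply, equal in both arms, and p1 and p0 the true proportions fulfilling it among the rest. Coded 0, the observed proportions are (1 − q)p1 and (1 − q)p0. Coded 1, they are q + (1 − q)p1 and q + (1 − q)p0. Either way the observed difference is (1 − q)(p1 − p0). The documents give no q. As q runs from 0 to 1, the retained fraction runs from all of the difference to none. The odds ratio also moves towards 1: coded 0, it goes from its true value towards p1/p0 as q rises.
- *Primary score.* Changing the coding from 0 to 1 adds one point to each patient concerned, so the arm means shift by q1 and q0 and their difference by q1 − q0. With equal shares this is 0.

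**The case against.** **The groups may overlap in practice.** The subgroup condition has no time window, while indicator 7 counts exacerbations per year, and the preceding year's exacerbations are asked about at both T0 and T1. If membership is fixed at T0 and indicator 7 is judged at T1, a patient with FEV1 above 50%, two exacerbations before T0 and fewer than two afterwards is in the subgroup and can be assessed. The 60% cut-off also opens a narrow overlap. This stands. A reader might infer that no patient in the subgroup score could ever be assessed on indicator 7. The article does not fix the timing and prints two cut-offs, so that reading goes too far, although 50% is the figure attached to the 13-item list.

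**The parenthesis may be one example of a wider item.** Elsewhere (Background, Clinical interventions/guideline adherence, the care bundle) appropriate drug treatment is described more broadly, with less steroid overuse as one part. On that reading 0–13 could stand. But the parenthesis is the only scoring criterion given, and none is given for the subgroup. Detail may be left to a full protocol; here the article itself fixes the item, the subgroup, the binary rule and the range, and these conflict.

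**No comparison is shown to be biased.** This stands for the subgroup score. A reader might also infer that inconsistent coding creates a spurious arm difference. Data collection procedures (under GPs) describes one independent research assistant entering the data, so nothing in the text supports that.

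**Other indicators may not apply either.** Ex-smokers are eligible, and indicators 1 and 2 concern smoking cessation. This is fair: the range of 0–12 treats those indicators as open to credit, and the missing rule for inapplicable indicators is wider than indicator 7.

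**Conclusion.** The point holds, with limits. As written, with both conditions judged at the same time and the 50% cut-off applied, indicator 7 is a constant in the 13-item score. The range is out by one point at one end: a maximum of 12, or a minimum of 1. The item tells the reader nothing about pharmacotherapy in that subgroup.

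The practical cost lies mainly in the separate analysis of indicator 7, where the difference in proportions shrinks by the factor 1 − q, assuming q is equal across arms and inapplicable patients are kept in with a fixed code. The primary score has the same gap in definition. It would be tempting to set the one-point coding shift against the assumed difference of 1.5 indicators in the sample-size calculation. That shift is per patient, and the arm difference moves only by q1 − q0, so the documents do not support a claim that the primary comparison is distorted.

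The correction is cheap and worth making before data are seen.

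**What to change.** 1. Remove indicator 7 from the subgroup score and state its range as 0–12 (indicators 1–6 and 8–13).
2. Analyse indicator 7 separately, with only patients meeting its stated condition as the denominator.
3. State, before data are seen, one rule, identical in both arms, for scoring indicator 7 in the primary 0–9 score when it does not apply.
4. State the time point at which subgroup membership and indicator 7 are judged. The programme aims to reduce exacerbations, so a classification made at T1 could itself depend on the arm; this should be weighed when the time point is chosen.
5. Reconcile the 50% and 60% cut-offs, and the 'or' and 'and/or' wording, for the four added indicators. Which cut-off applies is for the sponsor to decide; no clinical criterion is proposed here. If the sponsor wants pharmacotherapy in the subgroup score, it needs to supply an item defined for that subgroup.

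The cost is a change of wording, with no new data. The downside is that the subgroup score is no longer simply the nine primary indicators plus four, and the text should say so. The separate analysis of indicator 7 will also rest on fewer patients, but only those for whom it has a meaning.

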#### Quality of life

We use the COPD Assessment Test (CAT). The CAT provides clinicians and patients with a reliable measure of overall COPD-related health status for the assessment and long-term follow-up of individual patients. The CAT is a validated short and simple patient-completed questionnaire that has been developed for use in routine clinical practice to measure the health status and grading the impact of COPD on patients’ life. The CAT is available in different languages (http://www.catestonline.org). It compromises eight simple questions, eight items on a scale of 0 to 5 with a total scoring range of 0 to 40; CAT score < 10 low impact, 10 to 20 medium impact and > 30 very high impact of COPD on a patient’s life [29].

### Measures at baseline and follow up

#### Baseline

Patient demographics: gender, age, race/ethnicity, employment status, and family background.

Clinical characteristics: comorbidities (predefined selection of frequent comorbidities cardiovascular, diabetes type II), BMI, smoking status, PYs smoking, respiratory symptoms cough, sputum, dyspnea and severity of dyspnea (Medical research council MRC dyspnea scale), spirometry (FEV1/FVC < 70%) and grade of severity (FEV1 > 80% GOLD I mild COPD, FEV1 50 to 80% GOLD II moderate COPD, FEV1 30 to 50% GOLD III severe COPD, FEV1 < 30% GOLD IV very severe COPD) according to GOLD guidelines. Burden of COPD in daily life assessed with the COPD assessment test (CAT). Current drug therapy, exacerbations and health care utilization in previous year due to pulmonary problems, including hospital admissions and emergency department attendances or unscheduled visits are also assessed.

### Follow-up

We use a data collection tool with clinical questionnaires for patients and GPs (each with an allocated corresponding code) to measure performance.

### Data collection procedures

#### Patient questionnaire

The patients will receive detailed written information on the aim of the study. After giving their written informed consent they will receive a questionnaire (T0) assessing gender, age, employment status, and family background, the CAT, information on respiratory symptoms (cough, sputum, dyspnea), and severity of dyspnea (Medical research council MRC dyspnea scale), smoking status, motivation to quit, exacerbations and health care utilization (including unscheduled visits, emergency department attendances and hospital admissions due to pulmonary problems). Patients are asked at T0 whether, in the previous year before study inclusion, they had received: advice to quit smoking, assessment and advice for physical activity or advice/referral to pulmonary rehabilitation, recommendation/application of influenza vaccination, patient education with defining COPD and information about the main causes, signs and symptoms, information on medication and using inhalation devices with face-to-face instruction and demonstration of inhalation technique, information on how to identify and manage an aggravation of symptoms (exacerbation) and an action plan for exacerbation management including medication adjustment for exacerbation treatment. In addition patients are asked whether they have received COPD support by community resources (lung associations, support groups) and other specialized health professionals. Patients are asked the same questions one year after study inclusion T1. They receive the questionnaires and stamped envelopes with the postal address of the university and are asked to return the questionnaire in the envelope to the university at T0, and T1 after 12 months.

Patients will also be informed that neither the GP nor the practice team has any possibility of obtaining knowledge of their answers.

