### Timeframe of the study

The recruitment of the 30 GPs is planned over two months between July and August 2013 (−T2).

Patient eligibility screening and patient inclusion is projected within a period of three months (−T1). The intervention courses will start subsequently.

Assessments will be made as described above, T0 baseline assessments start from the inclusion; at baseline, data regarding COPD management in the year before inclusion will also be assessed retrospectively from the patient charts and transferred anonymously to the study center.

Final measurements (T1) will be performed one year after the ‘QualiCCare’ intervention.

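### T1, the time point of the primary outcome, is counted from patient inclusion in one section and from the training in another; the two dates differ by about 0 to 3 months per patient, plus any gap before the courses

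*Protocol article*

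**What the plan says.** The primary outcome is the difference in fulfilled care indicators "after one year between COPD patients in the intervention and control group as reported by the patient". The starting point of that year is not named there.

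Two other sections name it, and they differ:

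- **Patient questionnaire** (the instrument for the primary outcome): "Patients are asked the same questions one year after study inclusion T1".
- **Timeframe of the study**: "Final measurements (T1) will be performed one year after the ‘QualiCCare’ intervention".

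The Timeframe section also fixes the order of events. "Patient eligibility screening and patient inclusion is projected within a period of three months", and then: "The intervention courses will start subsequently". It ties the baseline to inclusion: "T0 baseline assessments start from the inclusion". No course date and no interval between the end of inclusion and the first course is given.

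On the recall period, the Patient questionnaire section says: "Patients are asked at T0 whether, in the previous year before study inclusion, they had received" the listed elements of care. For T1 it says only that the questions are the same.

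The GPs section speaks of 12 months and the Abstract of a one-year study period. Neither gives a starting point that would settle the matter. The Abstract and the section on recruitment of physicians state that control practices receive no training.

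**The concern.** Inclusion closes before training starts, so the two T1 rules give different dates for almost every patient. The primary outcome counts care delivered in a recalled year, and the date of the questionnaire decides which year that is.

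Under the inclusion rule, the recalled year in the intervention arm begins before the GP has been trained. Part of what is scored there is usual care, which pulls the arms together. Influenza vaccination, one of the nine indicators, is the clearest example. GP recruitment is planned for July and August 2013. If the three inclusion months follow directly, and if vaccination is given mainly in autumn (both assumptions), a patient included early would have the autumn 2013 vaccination counted, before training, and the first autumn after training would fall outside the window.

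Under the intervention rule, the recalled year in the intervention arm lies after training, but the reference event does not occur in control practices. The text does not say which date they use.

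The choice cannot be repaired at analysis. The T1 questionnaire is answered once, and the period it covers is fixed by when it is answered.

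**Working it through.** **1. Distance between the two dates.** Let *u* be the months from a patient's inclusion to the close of inclusion (0 to 3, from the Timeframe section), and *g* the gap between that close and the courses (not given).

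- Inclusion rule: T1 = inclusion + 12 months.
- Intervention rule: T1 = inclusion + *u* + *g* + 12 months.
- Difference = *u* + *g*: 0 to 3 months when *g* = 0, mean 1.5 if inclusion is uniform (assumption), and *g* more otherwise.

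**2. Pre-training share of the recalled year under the inclusion rule.** If T1 asks about the previous 12 months (inferred), the share in the intervention arm is (*u* + *g*)/12. With *g* = 0:

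- mean: 1.5/12 = 12.5%
- maximum: 3/12 = 25%

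**3. The plan's own sample size.** Inputs from Calculation of sample size: difference 1.5, SD 2.3, ICC 0.04, 8 patients per GP, 30 GPs, alpha 5% (taken as two-sided), power 90%.

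- n per arm without clustering = 2 × (1.960 + 1.282)² × 2.3² / 1.5² = 49.4, so 50
- design effect = 1 + (8 − 1) × 0.04 = 1.28
- n per arm = 50 × 1.28 = 64, or 128 in total

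The stated 240 is not reproduced. It exceeds what the inputs require for 90% power. That is a separate matter, but it explains the slack in step 4.

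**4. Effect on power.** With 120 per arm, the standard error of the difference is 2.3 × √(2 × 1.28/120) = 0.336. Power is approximately Φ(difference/0.336 − 1.960). Assumption, not in the document: the difference shrinks in proportion to the post-training share of the window.

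| Pre-training months | Difference | Power (normal) | Power (t, 28 df) |
|---|---|---|---|
| 0 | 1.5 | 99.4% | 99.1% |
| 1.5 (average) | 1.5 × 0.875 = 1.31 | 97.4% | 96.5% |
| 3 (every patient at the maximum) | 1.5 × 0.75 = 1.13 | 91.8% | 89.8% |

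**5. Gap at which the planned power is reached.** Power equals 90% at a difference of (1.960 + 1.282) × 0.336 = 1.09. That corresponds to 12 × (1 − 1.09/1.5) = 3.3 pre-training months on average. With a mean *u* of 1.5, the courses would have to start about 3.3 − 1.5 = 1.8 months after inclusion closes.

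**The case against.** The strongest reply is that the Timeframe section lists phases of the whole trial, so a year after the intervention can be read as one calendar point for both arms. That stands. A reader might infer that the control arm has no usable anchor, but the text supports only that none is stated; a shared workshop date would serve.

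A reader might also infer that the arms will be measured at different times. The document does not say so. The inclusion rule is the same for all patients, and unequal timing arises only if one rule were used in the intervention arm and the other in the control arm. Nor does the inclusion rule favour the intervention: its error runs toward no difference.

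Two further limits stand. The 12-month recall at T1 is inferred from the repetition of the questions. And proportional dilution fits binary indicators poorly, because a single visit after training can score an item for the whole year. The figure of 1.31 is therefore an illustration, and for many items the loss may be smaller. For vaccination it may be larger, but that is one indicator of nine and rests on assumed inclusion dates.

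Finally, an article may leave operational detail to the full protocol. That does not answer this point: the two sections both give the detail, and they disagree.

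**Conclusion.** The contradiction is in the current text and concerns the patient-reported primary outcome. The two definitions of T1 differ by about 0 to 3 months per patient, plus any gap before the courses, and no other section resolves them. Staff following different sections would collect different data.

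The consequence is mainly an undefined measurement period, with little lost power. Under the inclusion rule, and given the inferred recall, an average of 12.5% and at most 25% of the recalled year precedes training when the courses follow at once. On the protocol's inputs and proportional scaling, power stays at about 97% on average and 92% in the three-month worst case (just under 90% on the more cautious t calculation). A longer gap before the courses would lower it further.

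This should be fixed because the remedy is cheap and the timing cannot be recovered later. It does not invalidate the design, and the documents do not show that the arms will be timed differently.

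**What to change.** State one T1 rule for both arms. Name a single calendar index date tied to the courses, for example the date of the training workshop, or of the last one if there are several, and apply it equally to control practices. Send all T1 questionnaires 12 months after that date, with the recall written out as *in the last 12 months*. Align the Abstract (Methods), Patient questionnaire, GPs and Timeframe sections with this rule.

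The cost is protocol wording and mailing dates. The Trial status section says that patient recruitment had not started when the article was first submitted, so the change was feasible then.

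There are two drawbacks. Follow-up counted from inclusion becomes about 12 to 15 months, or slightly more if the courses are delayed, which no longer matches the stated one-year period. And the short interval between inclusion and the index date falls in neither the T0 nor the T1 recall window. Both should be stated openly in the protocol.
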